### Participant timeline {13}

#### Sample size {14}

Based on prior findings from 1 pilot study (intervention effect, unpublished) and 1 meta-analysis (control effect) [11], two a priori sample size calculations (1 conservative and 1 liberal method) were executed for the primary performance outcome “LVEF” by means of G*power v 3.1.9.2 (University of Kiel, Germany). As effect sizes for multivariate analysis are not available till now (partial ƞ^2^), the sample size calculation was executed based on baseline/follow-up differences between groups (Cohen’s *d*). For both calculations, an alpha risk of 0.05 and a statistical power of 0.8 were tolerated.

#### Conservative method

This method is considered the highest standard deviation found in both aforementioned studies. Assuming an effect size (Cohens d) of 0.678 for baseline/follow-up differences between groups (mean improvement; intervention: 10.4 ± 8.7, control 4.5 ± 8.7) on LVEF, 72 participants (36 intervention/36 control) were needed for statistical analysis with an adequate power, assuming an alpha risk of 0.05 (two-sided) and a beta risk of 0.20 (non-normal distributed). With an estimated loss to follow-up (mortality and dropout) of 10%, 80 patients have to be enrolled to ensure that 72 patients can be analysed.

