### Interim analyses {21b}

Two main analyses are planned: (a) An interim analysis when at least 20 participants per group had finished their 360-day follow-up for the primary endpoints, to assess the safety and to allow for an early halt to the recruiting process. (b) A final analysis after 80 patients. For both analyses, the significance level alpha will be set to 0.0294 according to the alpha spending plan proposed by Pocock.

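### The 72 evaluable patients are sized at a two-sided alpha of 0.05, but both analyses are tested at 0.0294; unadjusted power over the two looks is about 77%, not 80%

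*Protocol article*

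**What the plan says.** The Sample size section sets the planning targets: "For both calculations, an alpha risk of 0.05 and a statistical power of 0.8 were tolerated". The section explains that effect sizes for the multivariate analysis were not available, so the calculation rests on between-group differences in change, expressed as Cohen's d.

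The Conservative method, which the trial adopts, gives the inputs: "Assuming an effect size (Cohens d) of 0.678 for baseline/follow-up differences between groups", from "mean improvement; intervention: 10.4 ± 8.7, control 4.5 ± 8.7". It concludes that "72 participants (36 intervention/36 control) were needed for statistical analysis with an adequate power, assuming an alpha risk of 0.05 (two-sided") and, allowing 10% loss, that "80 patients have to be enrolled to ensure that 72 patients can be analysed". The error rates are given as "assuming an alpha risk of 0.05 (two-sided) and a beta risk of 0.20 (non-normal distributed").

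The paragraph that adopts the 80 patients (at the end of the Liberal method section) also adds an interim analysis at 20 versus 20. The Interim analyses section then fixes the testing level: "For both analyses, the significance level alpha will be set to 0.0294 according to the alpha spending plan proposed by Pocock". The hypotheses in the Efficacy analysis section are two-sided, and the main analysis is an ANCOVA adjusted for baseline LVEF.

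**The concern.** The sample size and the testing rule use different significance levels. The figure of 72 belongs to a design with one test at 0.05. The trial as planned has two tests at 0.0294. A Pocock boundary with unchanged maximum size costs power, because the final test is stricter and the early look returns only part of the loss. The article states both levels and does not reconcile them.

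What is at stake is how a non-significant result would be read. A reader would set it against a stated 20% chance of missing a 5.9-point difference, when on the plan's own inputs that chance is somewhat higher.

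**Working it through.** **Inputs, all from the article.** Mean changes 10.4 and 4.5, SD 8.7 in both arms, 36 per arm analysed, alpha 0.05 two-sided and power 0.80 (Sample size and Conservative method); interim at 20 per arm and 0.0294 at each look (Interim analyses).

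**1. Reproduce the plan's figure.**
- d = (10.4 − 4.5)/8.7 = 5.9/8.7 = 0.678.
- Two-sample t-test with n per arm: noncentrality = d·√(n/2). For n = 36 this is 0.678 × √18 = 2.877, with 70 degrees of freedom.
- At two-sided 0.05 the critical value is 1.994 and power is 81.0%. With 35 per arm it is 79.9%.
- So 36 per arm is the smallest size that reaches 80%, and 72/0.9 = 80 enrolled. The stated number reproduces as a single-look, unadjusted, normal-theory t-test at 0.05.

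**2. Same patients, final test at 0.0294.** The noncentrality stays at 2.877 and the critical value rises to 2.224. Power of the final test taken alone is 74.2% (75.8% by normal approximation).

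**3. Power of the two-look design.** The trial succeeds if it rejects at 20 per arm or at 36 per arm, each at 0.0294. The two statistics correlate at √(20/36) = 0.745.

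| Quantity (d = 0.678, looks at 20 and 36 per arm) | t-tests | Normal approximation |
|---|---|---|
| Interim alone | 46% | 49% |
| Final alone | 74% | 76% |
| Either look | 76.3–76.6% (simulated) | 78.0% |
| Overall type I error (d = 0) | 0.048–0.050 (simulated) | 0.049 |

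Overall type II error is therefore 1 − 0.766 to 1 − 0.763, or about 23–24% (22% by normal approximation), against the stated 20%.

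**4. Scale of the gap.** Two-look power of 80% would need about 40 per arm evaluable (39 gives 79.8–79.9%, 40 gives about 81%), or 38 per arm by normal approximation. That is 80 or 76 evaluable against 72.

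**5. Possible gain from baseline adjustment (assumption, shown as a range).** If baseline LVEF correlates with the change at r, adjustment reduces the SD by √(1 − r²), so the effective d is 0.678/√(1 − r²). Treating the adjusted comparison as a t-test with this d, the simulated two-look power is:

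| Absolute r, baseline with change | Two-look power |
|---|---|
| 0 | about 77% |
| 0.25 | about 79% |
| 0.30 | 80–81% |
| 0.40 | about 84% |

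The same can be put in terms of the correlation ρ between baseline and day-360 LVEF. With equal variances, r = √((1 − ρ)/2) in absolute value. Then ρ = 0.5, 0.7 and 0.8 give about 88%, 83% and 81%, and ρ = 0.85 gives just under 80%. The article states neither r nor ρ.

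**The case against.** The strongest reply is that the planned analysis is not an unadjusted t-test. It is an ANCOVA on baseline LVEF, and a moderate correlation would restore two-look power to 80% or more. This stands as a limit on the finding: a real shortfall in the planned analysis has not been shown. It does not rescue the stated figure, because the article says that the number rests on unadjusted differences and gives no correlation. The Mann-Whitney fallback would not carry the same adjustment.

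A second reply is that 80 patients are enrolled, and complete data on all of them would give about 81% over two looks. But the plan itself expects 72 to be analysable, and values carried forward are not full information.

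A third reply is that 3 to 4 points of power is less than the uncertainty in an effect taken from an unpublished pilot. That is fair and bears on severity, but not on whether the two sections agree.

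Three stronger readings are tempting and are not supported:
- **Type II error of 26%.** This treats the final look as if the interim did not exist. The design's error is the cumulative 23–24%.
- **Too few patients for a rank test.** The article's words on non-normality might suggest that 36 per arm misses 80% for a Mann-Whitney test even at 0.05. That depends on a parent distribution the article does not name, and some heavier-tailed shapes give more than 80%. All that can be said is that 72 reproduces as a normal-theory t-test number.
- **Inflated false-positive risk.** Two looks at 0.0294 hold the overall level at about 0.05.

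**Conclusion.** The point holds in a limited form. The article's sample size and its testing levels do not match, and on its own unadjusted assumptions (difference 5.9 points, SD 8.7, 36 per arm, looks at 20 and 36 per arm) the power is about 76–77% over both looks, or 78% by normal approximation, instead of the stated 80%. Type I error is sound.

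The shortfall of 3 to 4 points is modest. It could vanish under the planned ANCOVA if baseline LVEF correlates with the change at roughly 0.3 or more in absolute value, which is an assumption and not a documented input. It should be fixed, but it does not affect the validity of the test.

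**What to change.** Replace the power statement in the Conservative method with wording such as:

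> With 72 evaluable patients and Pocock levels of 0.0294 at the interim and final analyses, overall power is about 77% for a 5.9-point difference with SD 8.7, before any gain from baseline adjustment.

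Add that the planned ANCOVA could bring this to 80% or more if the baseline–change correlation is about 0.3 or more in absolute value, and label that as an assumption. It would also help to say that 72 is a t-test figure.

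The cost is a text change and a slightly less favourable power figure. Recruitment closed on 01.06.2022, so no additional patients are asked for, and the tests and boundaries stay as they are.

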#### Liberal method

This method considered the lowest standard deviation for each group type (control vs. intervention) found in both aforementioned studies. Assuming an effect size (Cohen’s d) of 0.903 for the baseline/follow-up differences between groups (mean improvement; intervention: 10.4 ± 7.22, control 4.5 ± 5.76) on LVEF, 32 participants (16 intervention/16 control) were needed for statistical analysis with an adequate power, assuming an alpha risk of 0.05 (one-sided) and a beta risk of 0.20 (normal distributed). With an estimated loss to follow-up (mortality and dropout) of 10%, 36 patients have to be enrolled to ensure that 32 patients can be analysed.

To ensure sufficient statistical power, 80 participants (conservative method) will be implemented in this study. Nevertheless, due to ethical considerations (i.e. implement not more participants than necessary), an interim analysis will be executed after 20 vs. 20 participants have been taken into account (10% above the liberal method) in order to stop the recruiting process when sufficient statistical power has been reached.

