## Statistical methods

### Statistical methods for primary and secondary outcomes {20a}

#### Efficacy analysis

The primary efficacy variable is the LVEF absolute change from baseline, i.e. the intra-patient difference or change between the pre-treatment (baseline) value day 0 and the value measured at day 360. This variable is quantitative and continuous and will be presented as a mean value with 95% confidence intervals. Change in mean (μ) LVEF from baseline to day 180, defined as delta ΔLVEF, will be analysed using an analysis of covariance (ANCOVA) adjusted for LVEF at baseline (as outlined in Guideline on adjustment for baseline covariates in clinical trials EMA/CHMP/295050/2013, 5.6 ‘change from baseline’ analyses) The main study hypotheses will thus be formulated as:

$$\begin{array}{c}\mathrm H0:\;\mathrm\mu\;\;\mathrm{{\triangle}LVEFcontrol}\;=\;\mathrm\mu\;\;\mathrm{{\triangle}LVEFshockwave}\\\mathrm H1:\;\mathrm\mu\;\;\mathrm{{\triangle}LVEFcontrol}\;\neq\;\mathrm\mu\;\;\mathrm{{\triangle}LVEFshockwave}\end{array}$$

In case of severe deviations from a normal distribution, the change in LVEF from baseline to day 360 will be analysed with the non-parametric Mann-Whitney U test.

Additionally, ANOVA for repeated measurements will be applied in order to analyse LVEF changes across the full study period (day 0, day 180, day360).

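### The 72 patients of the conservative method are labelled as a calculation for non-normal data, but 36 per arm is the ordinary t-test size under normality and contains no rank-test allowance

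*Protocol article*

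**What the plan says.** Under Sample size {14}, the protocol article reports two calculations made in G*Power for the LVEF outcome, for which "an alpha risk of 0.05 and a statistical power of 0.8 were tolerated".

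- **Conservative method.** "Assuming an effect size (Cohens d) of 0.678 for baseline/follow-up differences between groups", the article concludes that "72 participants (36 intervention/36 control) were needed for statistical analysis with an adequate power". The improvements behind the effect size are given as "mean improvement; intervention: 10.4 ± 8.7, control 4.5 ± 8.7". The error rates and the distribution are stated in these words: "assuming an alpha risk of 0.05 (two-sided) and a beta risk of 0.20 (non-normal distributed"). Ten per cent loss takes 72 to 80 enrolled. This is the size adopted.
- **Liberal method.** With an effect size of 0.903 it arrives at 16 per arm, "assuming an alpha risk of 0.05 (one-sided) and a beta risk of 0.20 (normal distributed").

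Neither paragraph names the test. The Efficacy analysis section makes baseline-adjusted ANCOVA the primary analysis. If the distribution departs severely from normal, "the change in LVEF from baseline to day 360 will be analysed with the non-parametric Mann-Whitney U test". The Interim analyses section sets the significance level at 0.0294 for both the interim and the final analysis.

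**The concern.** The two methods carry opposite distributional labels, so the distribution looks like one of the things that separates them. The Mann-Whitney test is the article's stated remedy for non-normal data. A reader would therefore take the 72 to include an allowance for a rank test.

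If the 72 is really a t-test figure, the basis printed beside the trial's adopted sample size is not the one that produced it. The 80% power would then be credited to a situation that was never calculated. This matters most if the fallback is used and gives a null result, because readers would judge that result against a power figure belonging to another test.

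**Working it through.** **Inputs (Conservative method, unless noted).** Means 10.4 and 4.5, common SD 8.7, two-sided alpha 0.05, power 0.80, 1:1 allocation (Sequence generation), 10% loss. The effect size reproduces: (10.4 − 4.5)/8.7 = 5.9/8.7 = 0.678.

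**Step 1: reproduce the printed size with a t-test.** Power is the probability that a noncentral t variable with 2n − 2 degrees of freedom and noncentrality d√(n/2) falls outside the two-sided critical values.

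- n = 36: noncentrality 0.678 × √18 = 2.88, 70 degrees of freedom, critical value 1.994, power 81.0%.
- n = 35: power 79.8%.

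The smallest adequate size is 36 per arm, or 72 in total, and 72/0.9 = 80. The printed figures are reproduced exactly.

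**Step 2: check the liberal figure in the same way.** With d = 0.903 and one-sided 0.05, n = 15 gives 77.9% and n = 16 gives 80.3%, so 16 per arm. This is also exactly a t-test size. A Mann-Whitney calculation with a normal parent would give 17. The two methods therefore used the same kind of calculation despite their different labels.

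**Step 3: try the Mann-Whitney test.** Replace n by n × ARE, where ARE is the asymptotic relative efficiency against the t-test, and repeat Step 1.

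| Setting | ARE | n per arm for 80%, alpha 0.05 | Power at 36 per arm, alpha 0.05 | Power at 36 per arm, alpha 0.0294 |
|---|---|---|---|---|
| t-test, normal | 1 | 36 | 81.0% | 74.2% |
| Mann-Whitney, normal parent | 3/π = 0.955 | 37 | 79.1% | 72.0% |
| Mann-Whitney, minimum efficiency | 0.864 | 41 | 74.9% | 67.1% |
| Mann-Whitney, logistic parent | π²/9 = 1.097 | 33 | 84.5% | 78.5% |
| Mann-Whitney, Laplace parent | 1.5 | 24 | 93.7% | 90.4% |

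Of these settings only the t-test gives 36.

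**Step 4: check by simulation** (36 per arm, pure location shift of d, two-sided 0.05, 20,000 runs per shape).

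| Shape | t-test | Mann-Whitney |
|---|---|---|
| Normal | 81.3% | 79.3% |
| Uniform | 81.0% | 75.5% |
| Parabolic (least favourable) | 80.7% | 74.8% |
| Logistic | 81.4% | 84.1% |
| Laplace | 81.1% | 90.3% |
| Exponential | 81.2% | 96.4% |

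The simulation confirms the light-tailed shortfall. It also shows the rank test gaining power for heavy tails and skew, although the asymptotic figure for Laplace is somewhat too high at this size.

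**The case against.** A reader might infer that the article promises 80% power for any non-normal distribution, and that the trial breaks this promise with a true power of about 75%. The documents do not support that reading, for four reasons.

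- The article defines its conservative method by the largest standard deviation in its two sources. It does not claim protection against the worst possible shape. Taking minimum efficiency as the standard is a reviewer's choice, and logistic or Laplace parents would need fewer than 36 per arm.
- Non-normal data do not in themselves reduce the power of the test that yields 36. The simulated t-test stays near 81% for every shape tried.
- The Mann-Whitney test is reserved for severe departures. For skewed or heavy-tailed shapes its simulated power at 36 per arm is above 80%: gamma(4) 85%, lognormal with sigma 0.5 93%, t with 5 degrees of freedom 87%, beta(2,5) 81%. The least favourable parabolic shape is hard to tell from normal. A Shapiro test on residuals rejected in only about 23% of simulated trials, so this shape would seldom trigger the fallback.
- The primary analysis is ANCOVA. If baseline and change correlate at an assumed 0.2 to 0.4, power at 36 per arm and alpha 0.05 is about 83% to 87%.

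All four points stand, and they limit the consequence. They do not rescue the label. It is also not a detail left to a fuller document, because the article prints a specific distributional basis beside a specific size and the two do not match.

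The 0.0294 test level is a separate and larger matter: it alone takes the t-test from 81.0% to 74.2% at 72 patients. The mislabelling exists at alpha 0.05 with a single look, and correcting alpha would not remove it.

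**Conclusion.** The stated basis of the 72 is wrong. It is the two-sample t-test size under normality, and no allowance was made for a rank test.

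The practical size is modest and confined to the Mann-Whitney fallback. At alpha 0.05 and 36 per arm, the gap to the stated 80% is 80 − 79.1 = 0.9 points for near-normal data and 80 − 74.9 = 5.1 points for the least favourable light-tailed shape. There is no shortfall for the skewed and heavy-tailed shapes examined.

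These figures assume a pure location shift of 0.678 standard deviations and 72 evaluable patients. The minimum-efficiency value is an asymptotic bound, so 75% should not be read as a finite-sample guarantee, nor as the power of the trial as it will be tested at 0.0294. The 0.0294 figures assume a two-sided test, in line with the article's two-sided alternative hypothesis.

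**What to change.** In the Conservative method paragraph, replace the non-normal label with: two-sample t-test, normal distribution. Drop any implication that 72 allows for non-normality.

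If power for the Mann-Whitney fallback is to be quoted, name the parent distribution and give the figure at the 0.0294 level of the Interim analyses section. At 36 per arm this is about 72% for a normal parent and about 67% at minimum efficiency (asymptotic approximation), beside about 74% for the t-test. Do not state a floor of 75%.

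Keep 80 enrolled. The cost is wording only. Recruitment closed on 01.06.2022 according to the Trial status section, and nothing in the conduct of the trial needs to change.

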#### Liberal method

This method considered the lowest standard deviation for each group type (control vs. intervention) found in both aforementioned studies. Assuming an effect size (Cohen’s d) of 0.903 for the baseline/follow-up differences between groups (mean improvement; intervention: 10.4 ± 7.22, control 4.5 ± 5.76) on LVEF, 32 participants (16 intervention/16 control) were needed for statistical analysis with an adequate power, assuming an alpha risk of 0.05 (one-sided) and a beta risk of 0.20 (normal distributed). With an estimated loss to follow-up (mortality and dropout) of 10%, 36 patients have to be enrolled to ensure that 32 patients can be analysed.

To ensure sufficient statistical power, 80 participants (conservative method) will be implemented in this study. Nevertheless, due to ethical considerations (i.e. implement not more participants than necessary), an interim analysis will be executed after 20 vs. 20 participants have been taken into account (10% above the liberal method) in order to stop the recruiting process when sufficient statistical power has been reached.

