### Recruitment {15}

Patients are recruited from University Hospital for Cardiac Surgery, Medical University of Innsbruck, Innsbruck, Austria, starting in November 2018. No specific measurements will be taken. Given the structure of the Austrian health care system, this department is the only institution in the allocated region providing cardiac surgery. All patients with a reduced LVEF admitted to CABG surgery, as decided by the institutional heart team, will be screened for eligibility by the study investigators. The approximate recruitment rate is expected to be 20 patients per year.

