### Trial status

Date: 11.11.2022

Protocol version: 1.4

Effective Date: 13.10.2021

First Patient First Visit (FPFV): 28.11.2018

Trial status: Active, not recruiting

Recruitment closed on 01.06.2022

Last Patient Last Visit (LPLV) is expected in April 2023.

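### The sample size gives 80% power at two-sided 0.05, but both planned looks test at 0.0294: on the plan's own sizing method overall power is about 76–77%, for an early stop that spares at most about 16–20 of 80 patients

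*Protocol article*

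**What the plan says.** The Conservative method section of the protocol article gives the sizing: "mean improvement; intervention: 10.4 ± 8.7, control 4.5 ± 8.7) on LVEF, 72 participants (36 intervention/36 control) were needed", "assuming an alpha risk of 0.05 (two-sided) and a beta risk of 0.20 (non-normal distributed". For attrition it adds: "With an estimated loss to follow-up (mortality and dropout) of 10%, 80 patients have to be enrolled". The Liberal method section adopts this size ("80 participants (conservative method) will be implemented in this study") and introduces the interim: "due to ethical considerations (i.e. implement not more participants than necessary), an interim analysis will be executed". It places the interim at 20 versus 20 participants and says it may end recruitment.

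The section Interim analyses {21b} fixes the trigger: "An interim analysis when at least 20 participants per group had finished their 360-day follow-up for the primary endpoints". It gives two purposes, assessing safety and allowing recruitment to stop early. It sets alpha at 0.0294 for both this look and the final analysis, citing Pocock. Recruitment {15} says: "The approximate recruitment rate is expected to be 20 patients per year".

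**The concern.** The sample size calculation spends the whole two-sided 0.05 on one test. The analysis plan tests twice, each time at 0.0294, with the same 36 per arm at the end. Neither sample size section mentions the lower level, so the stated power of 0.80 describes a test that the plan does not use.

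Equal levels make sense when early stopping brings a large gain. Here the primary endpoint takes 360 days to mature, and the article describes no pause in recruitment meanwhile. Most patients will be enrolled before the interim data exist. At stake is a lower chance of detecting the planned LVEF effect at the end, in exchange for a modest saving in patients.

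**Working it through.** **Inputs.** Mean improvements 10.4 and 4.5, SD 8.7, 36 per arm analysed, two-sided 0.05, power 0.80, 10% loss (Conservative method); improvements 10.4 ± 7.22 and 4.5 ± 5.76, d = 0.903 (Liberal method); interim at 20 per arm after 360 days, 0.0294 at both looks (Interim analyses); 20 patients per year (Recruitment).

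**1. The plan's own figure.** d = (10.4 − 4.5)/8.7 = 5.9/8.7 = 0.678. A two-sample t-test (noncentral t, two-sided 0.05) needs 36 per arm for 80% power, 72 in total. 72/0.9 = 80. The stated size is reproduced. Power at 36 per arm is 81.0%. (A Mann-Whitney calculation with relative efficiency 0.955 gives 37 per arm, so the t-test is the closer match.)

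**2. Power of the two-look test as planned.** t-tests at 20 and then 36 per arm, rejecting if p < 0.0294 at either look, by simulation (400,000 runs):

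| Levels (interim / final) | d | Crosses at interim | Overall power |
|---|---|---|---|
| 0.0294 / 0.0294 | 0.678 | 46% | 76.5% |
| 0.0085 / 0.0467 | 0.678 | 28% | 80.5% |
| 0.0294 / 0.0294 | 0.903 | 72% | 95% |
| 0.0085 / 0.0467 | 0.903 | 54% | 96% |

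Overall type I error is 0.049 for the equal levels and 0.050 for the alternative, so both control it. The alternative interim level comes from O'Brien-Fleming-type spending at information fraction 20/36 = 0.556: 2 × [1 − Φ(1.96/√0.556)] = 2 × [1 − Φ(2.63)] = 0.0085. The final level is then about 0.0467.

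The cost of the equal levels in the sizing scenario is 81.0 − 76.5 = 4.5 percentage points, which takes power below the stated 80%.

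**3. What an early stop can spare.** Assume uniform accrual and no pause. Number enrolled when the data are complete = patients needed for 40 finishers + 20 × 360/365.25.
- No loss: 40 + 19.7 = 59.7 enrolled; 80 − 59.7 = 20.3 not yet enrolled.
- 10% loss: 40/0.9 = 44.4; 44.4 + 19.7, about 64.2 enrolled; about 15.8 not yet enrolled.
- 10% loss plus an assumed 3 months for cleaning and review (not in the article): about 69.2 enrolled; about 10.8 left.

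Sensitivity to the accrual rate, from no loss to 10% loss and without reporting lag: 15 per year gives about 55–59 enrolled, 25 per year about 65–69.

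**4. Cost of changing the levels, in patients.** The drop in stopping probability is 46% − 28% = 18 points at d = 0.678, and 72% − 54% = 18 points at d = 0.903. Multiplied by 16–20 patients, this is 0.18 × 16 = 2.9 to 0.18 × 20 = 3.6, so about 3–4 fewer patients spared on average in either scenario.

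**The case against.** **The power figure ignores the planned model.** The primary analysis is an ANCOVA adjusted for baseline LVEF, whereas 76–77% is for an unadjusted comparison of changes. This stands as a qualification. If baseline and change correlate at 0.3, 0.4 or 0.5 (assumed values), the two-look design has about 81%, 83–84% or 87%; at 0.2 it has only about 78%. The article gives no correlation and states that its own sizing used group differences in change, so its claim of 0.80 rests on the unadjusted method.

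**More than 36 per arm may be analysed.** The primary population is intention-to-treat with last observation carried forward. With 40 per arm and no dilution of the effect, the unadjusted two-look power is about 81%. But values carried forward from before day 360 need not show the full effect, and the plan itself counts on 72 analysable patients.

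**Pocock is a legitimate choice.** It controls type I error and favours early stopping, which fits the stated ethical aim. Under the liberal scenario power is about 95% either way. This stands: the choice of boundary is not an error. The error is that the stated power was not computed for it.

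**Stronger readings that the article does not support.** A reader might infer that the interim cannot serve its ethical purpose, or that a stop was meant to hold enrolment at 40. The article never promises 40, the look also serves safety, and sparing 16–20 of 80 patients is a real saving. The 20-versus-20 wording and the 360-day trigger are compatible. A reader might also take the trial-status dates as confirming the timing. They give neither an interim date nor a number enrolled, so they confirm nothing. The absence of a futility rule, or of a policy for patients still in follow-up after a stop, is no finding here, because a condensed article commonly leaves both to the full protocol or analysis plan.

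**Conclusion.** The point holds as a mismatch between the stated power and the planned test. In the scenario that set the sample size, two looks at 0.0294 give about 76–77% overall power, not 80%. This rests on d = 0.678, 20 then 36 analysed per arm, and the unadjusted comparison used for sizing. Baseline adjustment could close the gap, by an amount that the article does not allow one to state. The return on the equal split is small: at most about 16–20 patients spared, assuming uniform accrual at 20 per year and no pause, and fewer with any reporting lag. The loss is moderate and no type I error problem arises, but it can be removed without more patients.

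**What to change.** Provided no unblinded look has taken place, keep the interim at 20 per arm and replace 0.0294/0.0294 with O'Brien-Fleming-type levels at information 20/36, about 0.0085 at the interim and 0.0467 at the end. Recompute the levels if the numbers actually analysed differ. Overall power in the sizing scenario becomes about 80–81%. If the sponsor prefers the better chance of stopping early and keeps Pocock, restate the power as about 76–77% on the sizing method. If the sponsor relies on the ANCOVA to reach 80%, state the assumed baseline correlation.

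The cost is an amendment to the interim paragraph and a lower chance of stopping early: 28% instead of 46% at d = 0.678, 54% instead of 72% at d = 0.903, or about 3–4 fewer patients spared on average. The article's status section says "Recruitment closed on 01.06.2022", so accrual can no longer be changed. If an unblinded look has already been made, the levels should stay as they are and only the power statement should be corrected.

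### The interim look is sized on a one-sided 0.05 test and tied to reaching sufficient power, which cannot serve as a stopping boundary and does not match the 0.0294 level set for that look

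*Protocol article*

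**What the plan says.** All places are in the Protocol article.

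- **Sample size {14}, Conservative method.** The final size (36 per arm analysed, 80 enrolled) uses changes in LVEF of "intervention: 10.4 ± 8.7, control 4.5 ± 8.7", d = 0.678, "assuming an alpha risk of 0.05 (two-sided) and a beta risk of 0.20 (non-normal distributed").
- **Sample size {14}, Liberal method.** A second calculation (16 per arm analysed, 36 enrolled) uses "intervention: 10.4 ± 7.22, control 4.5 ± 5.76", d = 0.903, "assuming an alpha risk of 0.05 (one-sided) and a beta risk of 0.20 (normal distributed"). The trial adopts the conservative 80. It adds an interim at 20 versus 20, described as a tenth above the liberal figure, "in order to stop the recruiting process when sufficient statistical power has been reached".
- **Efficacy analysis (under {20a}).** The null hypothesis is equal mean LVEF change in the two arms; the alternative is that the means are not equal.
- **Interim analyses {21b}.** The look takes place once at least 20 per group have finished 360 days. It serves to assess safety and to permit an early halt to recruiting. "For both analyses, the significance level alpha will be set to 0.0294 according to the alpha spending plan proposed by Pocock". The sidedness of 0.0294 is not stated.
- **Trial status.** Recruitment closed on 01.06.2022.

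**The concern.** Two things are wrong as printed.

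First, the stopping clause names a quantity that cannot trigger a stop. Power is a function of an assumed effect, a sample size and an alpha level. On the planning assumptions it is known before the first patient is enrolled, and interim data do not change it. If it is instead re-estimated from the interim effect, it is only a transformation of the interim p-value. Neither version is an efficacy boundary, and {21b} describes the same look in terms of a significance level.

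Second, the size of the look is justified by a test that is not the one planned there: one-sided 0.05 in the sizing, 0.0294 against a not-equal alternative in the analysis.

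At stake is whether a decision to stop recruiting can be shown to follow a pre-specified rule. Neither section says in words that recruitment stops for efficacy only if p falls below 0.0294.

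**Working it through.** **Inputs.** Difference 10.4 − 4.5 = 5.9 points (both methods). SDs 7.22 and 5.76 (Liberal method); 8.7 in both arms (Conservative method). Target: "an alpha risk of 0.05 and a statistical power of 0.8 were tolerated" (Sample size {14}). Allocation 1:1 (Sequence generation {16a}). Alpha 0.0294 at both looks ({21b}).

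**Formula.** Two-sample t-test with n per arm: df = 2n − 2 and noncentrality δ = d√(n/2). Power is the noncentral-t probability beyond the critical value (both tails if two-sided).

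**Step 1: reproduce the plan's figures.**
- Liberal SD: √((7.22² + 5.76²)/2) = 6.53, so d = 5.9/6.53 = 0.903.
- n = 16: δ = 0.903 × √8 = 2.555, df = 30, one-sided 0.05 critical value 1.697, power 80.3%. The stated 16 per arm reproduces. 32/0.9 = 35.6, so 36 enrolled; 36 × 1.1 = 39.6, about 40, which gives the 20 versus 20.
- Conservative: d = 5.9/8.7 = 0.678. At two-sided 0.05 the t-test needs 36 per arm (power 81.0%); 72/0.9 = 80. This reproduces too.

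**Step 2: apply the level used at the interim.**

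| n per arm | d | Test | Power |
|---|---|---|---|
| 16 | 0.903 | one-sided 0.05 | 80.3% |
| 16 | 0.903 | two-sided 0.05 | 69.6% |
| 16 | 0.903 | two-sided 0.0294 | 60.9% |
| 20 | 0.903 | one-sided 0.05 | 87.7% |
| 20 | 0.903 | two-sided 0.0294 | 72.2% |
| 20 | 0.678 | two-sided 0.0294 | 46.0% |

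For 80% power at d = 0.903, two-sided 0.05 needs 21 per arm. Two-sided 0.0294 needs 24 per arm (48 analysed; 48/0.9 = 53.3, so 54 enrolled), against 32 and 36 stated.

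**Step 3: is 0.0294 two-sided?** With a critical value of 2.178 at both looks, the two-sided overall type I error is 0.050 at half the information and 0.049 at 40/72. So 0.0294 behaves as the two-sided Pocock level for two looks, in line with the not-equal alternative.

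**Step 4: what the power clause would mean if taken literally.** On planning assumptions, no interim result can satisfy or fail it. The remaining reading, which the protocol does not state, is observed power of at least 80%. That requires z ≥ z(1 − α/2) + 0.842. At α = 0.0294 this is 2.178 + 0.842 = 3.020, or p < 0.0025. At α = 0.05 it is 1.960 + 0.842 = 2.802, or p < 0.0051. On that reading alone, an interim p between about 0.0025 and 0.0294 would cross the {21b} level but not meet the power clause.

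**The case against.** Several points on the other side stand.

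- **Error control.** A reader might infer that a one-sided 0.05 test will be run at the interim and that type I error is inflated. The protocol does not say so. The one-sided calculation only fixes when the look occurs, and {21b} sets 0.0294 at both looks, which holds the overall error near 0.05.
- **Interim power.** An interim look need not have 80% power, and the article relies on the 80 patients for adequate power. It states no power for 20 versus 20 at 0.0294, so no printed interim power figure is wrong. What is wrong is the basis offered for the size.
- **Opposite decisions.** A reader might infer two proven rules that disagree. The disagreement in p-value thresholds exists only under the observed-power reading. The clause may be a loose description of purpose, with {21b} giving the decision level. That lessens the conflict but leaves a clause that cannot be applied.
- **Safety numbers.** A reader might infer that an early stop would leave only about 20 treated patients for the safety endpoint. The documents do not support this. At the expected 20 patients per year (Recruitment {15}), about 20 × (2 + 360/365) = 60 would be enrolled when 40 finish day 360, so about 30 treated. Stopping recruitment does not end their follow-up.
- **ANCOVA.** The 72% and 46% ignore the gain from baseline adjustment. If the baseline-change correlation were 0.2 to 0.5 in size (an assumption; the document gives none), replacing d by d/√(1 − r²) gives roughly 74% to 84% (d = 0.903) and 48% to 59% (d = 0.678).

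**Conclusion.** The point holds as a defect of wording and justification. The stopping clause is not a valid criterion and is inconsistent with {21b}. The basis for 20 versus 20 does not match the test applied there: on the liberal effect the underlying 16 per arm has about 61% power rather than 80%, and the planned 20 per arm about 72%, or 46% on the conservative effect.

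These figures assume an unadjusted t-test, the plan's own effects and SDs, 20 evaluable patients per arm, and a two-sided reading of 0.0294. That reading is inferred from the stated alternative and the Pocock constant, not from the text of {21b}. It should be corrected, but it does not undermine the trial's error control.

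**What to change.** 1. Delete the sufficient-power clause from the Liberal method section.
2. State one rule in {21b}: recruitment may stop early for efficacy only if the two-sided primary analysis of day-360 LVEF change gives p < 0.0294 in favour of shockwave. All patients already randomised are followed to day 360 and reported.
3. Replace the one-sided justification of 20 versus 20 with the power at two-sided 0.0294: about 72% (d = 0.903) and 46% (d = 0.678), labelled as t-test approximations that ignore the ANCOVA gain.
4. Because recruitment closed on 01.06.2022, rewording cannot alter a recruitment decision. The report should therefore say whether the interim was run, which rule was applied and what followed from it.

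The cost is a few sentences and a less favourable stated power for the interim. No extra patients or data are needed.
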